## 3.2 Secondary objective

Secondary objective is to determine oral health-related quality of life of patients with the validated OHIP-G14 questionnaire, in order to be able to address the psycho-social component of disease. Results of questionnaires are compared with variables of facial nerve palsy, such as duration and cause of disease, which are collected as part of routine examination of Jena Facial Nerve Centre, as well as with values of a control group.

# 4. Study design and description

## 4.1 Type of study

The planned study is a controlled cross-sectional study.

## 4.2 Type of therapy assignment

No therapies will be performed on patients in sense of a study-related intervention. Routine dental examinations will be performed as indicated.

If desired, patients can receive expert advice for optimal oral care from the dentist during or after the examination and clarify open questions.

## 4.3 Type of comparison group

A corresponding control group of volunteers not suffering from facial nerve palsy will be recruited in exactly the same way as the patient group from the setting of ambulance level and ward level of the ENT-clinic of Jena University Hospital.

In event that too few controls can be recruited from this setting for good comparability, study-related examinations are carried out on corresponding controls from Tinnitus Centre of the ENT- clinic of Jena University Hospital or on patients from dental practices established in Thuringia.

The study will be matched according to age and gender.

## 4.4 Scope of the study

A total of 60 patients and 60 controls will be included. The exact sample size was planned with the Institute for Medical Statistics, Informatics and Data Science Jena using the programme G*power.

## 4.5 Patient and subject recruitment

Both collectives will be recruited and examined by the same examiner.

Patients are recruited from the ENT-clinic of Jena University Hospital during EMG consultation hours on Tuesdays, within the framework of part-time inpatient facial nerve palsy training of Jena Facial Nerve Centre and patients with acute facial nerve palsy within the inpatient stay.

Recruitment of suitable controls also takes place in the ENT-clinic of Jena University Hospital. Controls will be included who are undergoing inpatient treatment but not due to facial nerve palsy. Suitable controls must also not have suffered facial nerve palsy in their past. Furthermore, an attempt will be made to recruit patients via the Tinnitus Centre at Jena University Hospital. Furthermore, patients can be recruited from dental practices established in Thuringia, if this is necessary for a better comparison result to the patient group.

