## 1.3 Synopsis

| **Title of the study** | Oral health and oral health-related quality of life of patients with facial nerve palsy at Jena University Hospital |
| --- | --- |
| **Short name of the study (acronym)** | Oral health and oral health-related quality of life |
| **Head of study** | Priv.-Doz. [name] [name] |
| **further head of study** | Priv.-Doz. Dr. med. dent. [name] |
| **Investigator** | cand. med. dent [name] |
| **Indication/target population/disease** | Controls: healthy persons without facial nerve palsy ever diagnosed by a doctor  Patients: patients with different forms of facial nerve palsy in different temporal stages/ with different disease duration |
| **Study design/methodology** | Controlled cross-sectional study |
| **Clinical trial objectives/Objectives** | Primary objective:  To record oral health and oral health-related quality of life in patients and controls:  - To record dental status  (tooth mobility, restorations)  - To assess periodontal health  (PSI, presence of calculus, attachment loss and MPD)  - Assessment of gingiva bleeding  - Assessment of caries  (PUFA index and caries activity)  - Assessment of plaque infestation  (TI and API)  - Detection of oral mucosal abnormalities  - Detection of halitosis  Secondary objective:  - To assess oral health-related quality of life |
| **Target variables/criteria/endpoints** | Primary target variable:  PSI (chronic periodontitis parameter).  MPD (maximum probing depth)  mod. SBI (parameter for bleeding tendency)  PBI (parameter for quantity of papillary bleeding)  PUFA (parameter for odontogenic infections due to untreated caries)  API (parameter for approximal / interdental plaque infestation)  TI (parameter for plaque infestation)  Secondary target variable:  Oral health-related quality of life |
| **Number of participants** | 60 patients an 60 controls |
| **Total number of participants** | n=120 |
| **Inclusion criteria** | Controls: no history of facial nerve palsy, matched with patients according to age and gender  Patients: patients with all forms of facial nerve palsy (diagnosed by a doctor) |
| **Exclusion criteria** | Multimorbid patients/controls  Lack of informed consent  Edentulous patients/controls  Patients/controls with following diagnosed diseases:  - Haemophilia A and B  - Epilepsy  - AIDS |

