**Controls**

- multimorbid subjects
- age and gender mismatch with previously studied patients
- diagnosed facial nerve palsy currently or in past
- lack of consent from control or legal guardian (for subjects under 18 years of age) to participate in study
- edentulous
- suffering from one of following diagnosed diseases: Haemophilia A and B, Epilepsy, Aids

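### The rule on admission reason lets an ENT inpatient treated for oral or dental disease serve as a control, which may shrink the patient-control difference

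*Protocol*

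**What the plan says.** Protocol 4.5 gives one rule on why a ward control is in hospital: "Controls will be included who are undergoing inpatient treatment but not due to facial nerve palsy". The next sentence adds a history rule: "Suitable controls must also not have suffered facial nerve palsy in their past".

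Protocol 5.2 (Controls) repeats the palsy bar ("diagnosed facial nerve palsy currently or in past"). It also excludes "multimorbid subjects", a term it does not define, as well as edentulous persons, those who do not match on age and gender, those without consent, and anyone "suffering from one of following diagnosed diseases: Haemophilia A and B, Epilepsy, Aids".

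The synopsis (1.3) describes the group differently: "Controls: healthy persons without facial nerve palsy ever diagnosed by a doctor".

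Protocol 4.3 says controls are "recruited in exactly the same way as the patient group from the setting of ambulance level and ward level of the ENT-clinic", that is, from outpatients and inpatients. The Tinnitus Centre and dental practices are further sources. Matching is on age and gender.

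The outcomes in 1.3, 3.1 and 3.2 include PSI, probing depth, bleeding, plaque, mucosal findings, halitosis, OHIP-G14 and "PUFA (parameter for odontogenic infections due to untreated caries"). The summary (1.2) names periodontal health, measured by PSI, as the primary criterion.

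**The concern.** Hospital controls should not be in hospital because of the outcome under study. If they are, the control group carries more of that outcome than the population it stands for. Under 4.5 and 5.2, an ENT inpatient treated for an odontogenic infection, an oral mucosal lesion or a salivary gland infection meets every written criterion, provided he or she has teeth, is not multimorbid and has never had a palsy. PUFA, mucosal findings, halitosis and OHIP-G14 are then partly determined by the way that person was selected.

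Matching on age and gender does not touch this. Questionnaire 1 (6.2) collects risk factors for poor oral hygiene, but no rule uses them to exclude a control. The expected direction is towards no difference, and a larger sample would not remove the bias. The study could then report no deficit where there is one, although finding such a deficit is its stated purpose in 2.2.

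**Working it through.** **1. The eligibility text side by side.**

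| Place | What it requires of a control | Stops an admission for oral, dental or salivary disease? |
|---|---|---|
| 4.5 | Not admitted for palsy; no past palsy | No |
| 5.2 (Controls) | Not multimorbid, not edentulous, matched, consenting, no haemophilia, epilepsy or AIDS | No; a single acute infection need not be multimorbidity |
| 1.3 Synopsis | Healthy, never diagnosed with palsy | Arguably yes, but it conflicts with recruiting inpatients |

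**2. The plan's own sample size.** Inputs from section 7: two-sided Wilcoxon-Mann-Whitney test, min ARE (0.864), d = 0.6666667, alpha 0.05, power 0.80, allocation 1:1. With the noncentral t approximation:

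- df = 2 × 0.864 × n − 2
- noncentrality = d × √(0.864 × n / 2)
- n = 43 gives power 0.809, so the stated 43 per group reproduces
- n = 60 gives 0.92 if all 60 are analysed

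No stated figure is wrong. The point is about who the controls are.

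**3. What affected controls do to the difference.** Let a fraction f of controls be worse than the other controls by s SD. The difference left is d − f × s. The documents give neither f nor s; both are assumed here.

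| Assumed s | f | Controls affected, of 60 | Difference left (SD) | Power, 60 per group |
|---|---|---|---|---|
| – | 0 | 0 | 0.667 | 0.94 |
| 0.667 (as bad as patients) | 10% | 6 | 0.667 − 0.067 = 0.600 | 0.88 |
| 0.667 | 20% | 12 | 0.667 − 0.133 = 0.533 | 0.80 |
| 1.5 | 10% | 6 | 0.667 − 0.150 = 0.517 | about 0.77 |
| 1.5 | 20% | 12 | 0.667 − 0.300 = 0.367 | about 0.47 |

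The power column comes from simulating the rank test with normal data. In the last two rows it moves by 0.01 to 0.02 between runs and with whether the number affected is fixed or random.

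**4. Cross-check with the plan's conservative method.** For s = 0.667, dividing the remaining difference by the pooled SD of the mixture gives d = 0.594 (10%) and 0.524 (20%). The min ARE method then gives 0.92, 0.85 and 0.75 at 60 per group for f = 0, 10% and 20%. At 43 per group it gives 0.81, 0.71 and 0.61. It starts lower than the simulation because min ARE is a worst-case efficiency; the pattern is the same.

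**The case against.** - **The synopsis says healthy.** On that wording a person with a dental abscess is arguably not a valid control. This stands in part: it turns the gap into a conflict within the protocol. But 4.5 expressly recruits inpatients, and the eligibility lists in 5.1 and 5.2 do not require a control to be healthy.
- **Palsy is not the only bar.** A reader might infer from 4.5 that nothing else excludes a ward control. That is wrong: past palsy, multimorbidity and the other items in 5.2 apply. None of them closes this gap.
- **Nothing shows that it happens.** The protocol lists no ward diagnoses, and wards are only one source of controls. A 20% share of all controls would mean a still larger share of ward controls. This stands, so the shares above are illustrations only.
- **The 1.5 SD case is severe.** It makes affected controls 1.5 − 0.667 = 0.83 SD worse than the palsy patients. With the milder shift, a 10% share leaves power at 0.88. This stands, particularly for PSI.
- **The same-clinic design is deliberate.** Patients enter with any form of palsy and are not excluded for concurrent oral disease. Removing every control with oral disease would make controls healthier than their source and push the difference the other way. This stands and limits the fix: the rule should look only at the reason for admission.

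**Conclusion.** The concern holds as a risk of unknown size. The written rules allow persons admitted for a measured outcome into the control group, and the synopsis contradicts those rules. The likely direction is towards zero. The effect is probably larger for PUFA, mucosal findings, halitosis and OHIP-G14 than for PSI.

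Under the assumed shares of 10% and 20%, power at 60 per group goes from about 0.94 to 0.88 and 0.80 if affected controls resemble patients, and to about 0.77 and 0.47 if they are 1.5 SD worse than other controls. These figures rest on normal data, the planned d of 0.667, all 60 per group analysed, and f and s chosen for illustration.

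A reader might go further and conclude that such controls are present and that a true deficit is being hidden. The documents do not support that. They give no admission diagnoses, no prevalence of PUFA findings and no evidence that odontogenic infections are treated on this ward. Many ENT admissions would leave oral health unaffected.

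**What to change.** 1. Reconcile the synopsis (1.3) with 4.5, so that both describe the same control population.
2. In 4.5 and 5.2 (Controls), state that a ward control is not eligible if the reason for the current admission is a disease of the teeth, jaws, oral cavity or salivary glands, or an odontogenic infection. Limit the rule to the reason for admission; concurrent oral disease should not exclude a control.
3. Record each control's admission diagnosis and source (ward, outpatient, Tinnitus Centre, dental practice). The findings sheet is not among the pages at hand; if it already has these items, nothing need be added.
4. For controls already examined, add a sensitivity comparison without those who fail the rule. Either adjust for age and gender or drop the whole matched pair, so that the matching is respected.

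The cost is one eligibility sentence, two recorded items that should be available from clinic records, and one extra analysis. The downside is a smaller pool of ward controls; other ENT admissions, outpatients and the Tinnitus Centre remain available.

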## 6.3 Oral examination

Oral examination of patients follows the same procedure as that of controls.

During oral examination, the examiner inspects the well-lit oral cavity and diagnoses teeth, gingiva and oral mucosa as well as existing dentures as oral structures. A complete dental status of the person including tooth restorations and their tooth mobility, periodontal health by means of PSI, presence of calculus, MPD as well as attachment loss, gingival bleeding by means of mod. SBI according to Lange et. al 1986 and PBI according to Mühlemann and Saxer 1975, caries infestation using PUFA index according to Monse et al. 2010 and caries activity, plaque infestation using API according to Lange et al. 1986 and TI according to Turesky et al. 1970, abnormalities in oral mucosa according to WHO classification and presence of halitosis were examined and documented. A paper-based report form (see appendix) is used to record and document the dental status and various oral health parameters, which is converted into an Excel document later. After findings have been recorded, intraoral photographs are taken.

If desired, patients can ask the examiner open questions regarding oral care and receive expert advice for optimal tooth cleaning and plaque management.

Examinations are carried out on premises of ENT department at Jena University Hospital. An examination of controls is also conceivable in a dental practice. Participating patients and controls will be examined and treated in a standardized manner in the ENT-clinic of Jena University Hospital with regard to their illness independently of the planned study. Data obtained on oral health of patients/controls will be communicated to them and treated confidentially, but will have no influence on further dental and ENT treatment of patients.

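### Controls may be drawn from dental practices, a source tied to the oral-health outcomes, under triggers that differ between sections; the patient-control difference can be biased as far as this source is used

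*Protocol*

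**What the plan says.** Protocol section 4.3 states that the control group "will be recruited in exactly the same way as the patient group from the setting of ambulance level and ward level of the ENT-clinic". Its next paragraph opens a fallback to the Tinnitus Centre or to Thuringian dental practices: "In event that too few controls can be recruited from this setting for good comparability". Matching is on age and gender.

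Section 4.5 names three routes for patients: an outpatient clinic ("Patients are recruited from the ENT-clinic of Jena University Hospital during EMG consultation hours on Tuesdays"), a part-time inpatient training programme, and inpatient stays for acute palsy. For ENT controls it says: "Controls will be included who are undergoing inpatient treatment but not due to facial nerve palsy". It adds the Tinnitus Centre without a condition, and then dental practices: "patients can be recruited from dental practices established in Thuringia, if this is necessary for a better comparison result to the patient group". Section 1.2 repeats both extra sources, for the sake of comparability.

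Section 6.3 places examinations on the ENT premises but adds: "An examination of controls is also conceivable in a dental practice". The synopsis (1.3) describes the group as "Controls: healthy persons without facial nerve palsy ever diagnosed by a doctor".

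The primary variables in the synopsis are PSI, maximum probing depth, two bleeding indices, PUFA and two plaque indices. Neither the eligibility criteria (5.1, 5.2) nor the recruitment sections restrict recent dental treatment or the reason for a dental visit, and no limit is set on how many controls may come from practices.

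**The concern.** A control group should show what the patients' oral health would look like without palsy. Palsy patients reach this study through ENT care, whatever their dental habits. A person recruited in a dental practice is there for a check-up, for treatment or for a complaint, and each of these is linked to plaque, bleeding, probing depth and untreated caries. Two people of the same age and gender can differ widely in this respect, so the matching does not help.

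The direction cannot be known beforehand. Regular, recently treated attenders would make controls look healthier and exaggerate the difference. Complaint-driven attenders would make controls look worse and mask it. A larger sample does not cure either.

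Three further features add to this. The fallback has two differently worded triggers, so the person recruiting has discretion over the control source. The ENT control route in 4.5 is narrower than the one promised in 4.3. The place of examination may differ by group, and with it lighting and equipment for plaque, probing and caries findings.

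**Working it through.** **1. The sections side by side**

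| Item | 1.2 | 4.3 | 4.5 |
|---|---|---|---|
| ENT controls | Outpatient and ward level | Outpatient and ward level, same route as patients | Described as inpatients; outpatients not mentioned |
| Tinnitus Centre | Allowed, for comparability | Only if too few ENT controls | Attempted, no condition |
| Dental practices | Allowed, for comparability | Only if too few ENT controls | If needed for a better comparison result |
| Cap on practice controls | None | None | None |

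The dental-practice route is therefore common to all three sections. What differs is the condition that opens it and the care level of ENT controls.

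**2. The plan's own figure reproduced**

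Inputs from section 7: Wilcoxon-Mann-Whitney test, two groups, two-sided alpha 0.05, power 0.8, d = 0.6666667, min ARE, allocation 1:1. The minimum asymptotic relative efficiency is 0.864.

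Method: replace n per group by n' = 0.864 n. Then use the two-sample noncentral t distribution with df = 2n' − 2 and noncentrality d × √(n'/2).

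- n = 43: n' = 37.15, noncentrality 0.6667 × √18.58 = 2.87, power 0.809.
- n = 42: power 0.7998, just short of 0.8.

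So 43 per group is confirmed. At the planned 60 per group, n' = 51.84, noncentrality is 0.6667 × √25.92 = 3.39, and power is 0.920.

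**3. Illustration of the bias**

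Two quantities are not in the protocol and are assumed here: the share f of controls from dental practices, and the shift s (in SD) between such people and comparable people in the patients' own setting.

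Bias = f × s. The false-positive rate is the rejection probability of the planned test when the true difference is zero but the observed one is centred on the bias. For f = 0.5 and n = 60:

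- s = 0.2: bias 0.5 × 0.2 = 0.10; noncentrality 0.10 × 5.09 = 0.51; rate 8.0%.
- s = 0.5: bias 0.5 × 0.5 = 0.25; noncentrality 0.25 × 5.09 = 1.27; rate 24.3%.

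| f | s | Bias (SD) | Bias / 0.667 | False-positive rate | Power at d = 0.667 if bias opposes it |
|---|---|---|---|---|---|
| 0 | – | 0 | 0 | 5% | 92% |
| 0.25 | 0.2 | 0.05 | 7.5% | 5.7% | 88% |
| 0.25 | 0.5 | 0.125 | 19% | 9.7% | 78% |
| 0.5 | 0.2 | 0.10 | 15% | 8.0% | 82% |
| 0.5 | 0.3 | 0.15 | 22% | 11.8% | 74% |
| 0.5 | 0.5 | 0.25 | 37.5% | 24.3% | 56% |

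The calculation ignores the small extra spread of a mixed control group: f(1 − f)s² is at most 0.25 × 0.25 = 0.06 on a variance of 1. It also uses the unpaired test of section 7.

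**The case against.** Much can be said for the plan. The dental-practice route is conditional wherever it appears. One examiner recruits and examines both groups (4.5), and the examination follows the same procedure (6.3). Multimorbid people are excluded from both groups (5.2), which limits the worry about sicker inpatients. Questionnaire 1 records hygiene attitude, cleaning habits and risk factors, so a statistical analysis plan could adjust for them or for source. The comparison of the paretic with the non-paretic side (6.6, 6.7) is made within patients and does not depend on the controls at all. These points stand, and they bound the concern. They do not settle where controls come from, what opens the fallback or where controls are examined; the protocol fixes these before any data exist, and adjustment for reported habits would repair the selection only in part.

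Several stronger readings are tempting but not supported:

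- A reader might infer that dental-practice controls contradict 4.3. They do not: 4.3 itself announces that fallback. The tension with 4.3 concerns the inpatient wording and the differing trigger.
- A reader might infer that mainly outpatient patients are set against inpatient controls. Section 4.5 gives no proportions, two of its three patient routes are labelled inpatient, it does not say that controls are inpatients exclusively, and it also names the Tinnitus Centre.
- The trigger in 4.5 might be read as licence to choose controls by the result they give. Beside 1.2 and 4.3 it is more plausibly loose wording for comparability. The defect is that it is undefined.
- The arithmetic can be pushed to all controls coming from practices, with false-positive rates of 17.2% to 71.3%. That does not describe a plan in which ENT is the main source and practices a fallback.

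**Conclusion.** The concern holds as a risk built into the plan. Following the protocol as written, an unlimited number of controls may come from a source linked to the outcome, under a trigger stated in two ways, with age and gender matching unable to correct it and with an examination place that may differ by group. It cannot be said that the group difference is biased; it can be, to the extent the fallback is used, and the direction is open.

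The size rests wholly on assumed shares and shifts. With half the controls from practices and a shift of 0.2 to 0.5 SD, the bias is 15% to 37.5% of the planning effect and the false-positive rate is 8% to 24%. If the bias opposes a true effect of the planned size, power falls from 92% to between 82% and 56%. With a quarter from practices, the false-positive rate is 5.7% to 9.7%. The description of controls as healthy in the synopsis fits none of the named sources, but that is a clerical matter.

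**What to change.** - **4.5:** recruit ENT controls at both outpatient and ward level, in line with 4.3, and at the matched patient's care level where possible.
- **1.2, 4.3 and 4.5:** state one objective trigger for any fallback, namely that no age- and gender-matched ENT control was found. Use the Tinnitus Centre first.
- **Source:** record the recruitment source of every control. Keep dental-practice controls out of the primary comparison, or at minimum prespecify a sensitivity analysis without them.
- **6.3:** examine controls on the ENT premises where feasible, and record the place where it was not.
- **1.3:** replace the description of controls as healthy with one that fits the sources named.

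The cost is protocol wording and one recorded item per control. The sample size calculation is unchanged at 43 per group, with 60 planned. Control recruitment may be somewhat slower; the protocol gives no figures from which to say by how much, but ENT outpatients are already a permitted source under 1.2 and 4.3.

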## 1.2 Summary

Facial nerve palsy lead to immobility of the affected side of face (Trepel, 2017). Assumable, food residues on tooth surfaces cannot be removed by natural self-cleaning mechanisms such as targeted muscle movements or saliva, which are described in literature (Elferich & Tittmann, 2004). In addition to food intake, oral hygiene is impaired in patients (Jakobsen & Sticher, 2015). Deterioration of oral hygiene increases the risk of oral infections and consequently of other diseases (Hellwege, 2018).

Aim of this study is to investigate the oral health and oral health-related quality of life of patients with different forms of facial nerve palsy, as well as oral health in relation to facial nerve palsy variables such as disease duration and cause, which are collected as part of routine investigation at Facial Nerve Centre Jena.

In a controlled cross-sectional study, oral health parameters and oral health-related quality of life will be investigated at one time. Since patients in different temporal stages (acute phase, chronic phase) are to be documented, the setting of the Ears-, Nose- and Throat (ENT-) clinic Jena was chosen. There are both patients, with acute paresis and patients with chronic forms of facial nerve palsy. Oral health parameters and oral health-related quality of life of these patients groups should be compared with a control group. For this, controls without facial nerve palsy ever diagnosed by a doctor will be matched with corresponding patients according to age and gender.

Primary criterion for assessment of oral health will be the assessment of periodontal health, which will be analysed by a dentist using parodontal screening index (PSI; Hellwege, 2018; Weber, 2017). Other established indices are used to record caries and plaque incidence, bleeding tendency of gingiva, abnormalities of oral mucosa and presence of halitosis. These indices are compared between the two groups. Oral health-related quality of life will be assessed using the validated OHIP-G14- questionnaire (John, 2002; Slade 1997).

It is assumed a case number of 60 patients and 60 controls.

Both study groups will be recruited from ambulance level and ward level of ENT-clinic at Jena University Hospital. For better comparability, further controls can be recruited from the tinnitus centre of ENT-clinic Jena as well as from dental practices established in Thuringia.

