**Controls n=60**

- selection with regard to age and sex as a control group to previously examined patients
- no facial nerve palsy ever diagnosed
- written consent of the subject or legal guardian (for subjects under 18 years of age) to participate in the study
- toothed
- not suffering from any of the following diagnosed diseases: Haemophilia A and B, Epilepsy, Aids

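### The trigger for changing the control source is worded three ways, none of them measurable, and is applied by the examiner who scores both groups

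*Protocol*

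**What the plan says.** **Who recruits and scores.** Protocol section 4.5: "Both collectives will be recruited and examined by the same examiner".

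**When controls are chosen.** Section 5.1 (Controls) describes "selection with regard to age and sex as a control group to previously examined patients". Section 5.2 (Controls) excludes for "age and gender mismatch with previously studied patients". The patient's oral findings therefore exist before the matching control is sought.

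**When another source may be used.** Three sections deal with this:

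- Section 1.2: "For better comparability, further controls can be recruited from the tinnitus centre of ENT-clinic Jena", and also from dental practices in Thuringia.
- Section 4.3: "In event that too few controls can be recruited from this setting for good comparability", the tinnitus centre or dental practices are used.
- Section 4.5: recruitment through the tinnitus centre will be attempted, with no condition attached. Dental practices may be used "if this is necessary for a better comparison result to the patient group".

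**What limits the choice.** Matching is on age and gender. Section 5.2 also excludes "multimorbid subjects", a term the protocol does not define; the same exclusion applies to patients.

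**The concern.** The patient-control comparison is part of the primary objective (section 3.1). It is only as sound as the way in which controls enter the study. Here the person who chooses the control has already scored the patient, will score the control, and decides when to look elsewhere. The trigger for looking elsewhere is a judgement, and in section 4.5 it is worded as a judgement about the result of the comparison.

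If the choice among eligible persons, or the choice of source, followed an impression of oral health, the difference between the groups would be shifted. Healthier-looking controls would create or enlarge a difference; less healthy ones would hide it. Matching on age and gender does not prevent this, and adjusting for those factors later does not undo selection on the outcome.

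**Working it through.** **1. The three wordings side by side**

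| Section | Condition for leaving the ENT clinic | Status of tinnitus centre | Measurable? |
|---|---|---|---|
| 1.2 | to improve comparability | optional addition | no |
| 4.3 | too few controls for good comparability | fallback | no number, date or age tolerance |
| 4.5 | dental practices: a better comparison result; tinnitus centre: none | planned without condition | no |

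The sections disagree on what opens the other sources and on whether the tinnitus centre is a fallback. None gives a point at which two people would agree that the condition had been met.

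**2. What the examiner can know at that moment**

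- The patient's scores are known, by sections 4.5, 5.1 and 5.2 taken together.
- The control's formal scores are not. Consent and the first questionnaire precede the oral examination (sections 6.1, 6.2 and 6.8).
- An informal impression is possible. The examiner conducts the consent discussion, and visible teeth or halitosis, which is a study parameter, can be noticed there. For attenders of a dental practice, dental status may already be known.
- Findings accumulate in both groups in the hands of one person, since both inclusions begin in 08/2020 (section 4.6).

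The route is therefore indirect, but no stated rule closes it. The protocol gives no order of approach, no screening log and no separate person to select controls.

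**3. The plan's own figure**

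Section 7 gives 43 per group (Wilcoxon-Mann-Whitney, two-sided 0.05, power 0.80, d = 0.6666667, min ARE). With ARE = 0.864, the effective n is 43 × 0.864 = 37.15, the degrees of freedom are 2 × 37.15 − 2 = 72.3, and the noncentrality is 0.6667 × √(37.15/2) = 2.87. Power is 0.809, and 43 is the smallest n that reaches 0.80. The figure reproduces and is not affected by this point.

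**4. Illustration of size, on assumptions that are not in the protocol**

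Normal scores, no true difference, 60 per group, two-sided Wilcoxon-Mann-Whitney at 0.05, 5,000 simulated studies.

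(a) Selection shifts control scores by a fixed amount:

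| Shift (SD) | 0 | 0.1 | 0.2 | 0.3 | 0.5 |
|---|---|---|---|---|---|
| Rejection rate | 0.05 | 0.09 | 0.18 | 0.35 | 0.76 |

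(b) In a fraction q of pairs, the healthier-looking of two eligible persons is taken, and appearance correlates r with the index. The better of two standard normal values lies 0.564 SD from the mean on average, so the expected shift is q × r × 0.564. For q = 0.5 and r = 0.3, 0.5, 0.7 this is 0.085, 0.141 and 0.197 SD (simulated: 0.083, 0.145 and 0.199).

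| | r = 0.3 | r = 0.5 | r = 0.7 |
|---|---|---|---|
| Rejection rate, q = 0.5 | 0.07 | 0.12 | 0.19 |
| Rejection rate, q = 1 | 0.15 | 0.33 | 0.58 |

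The values of q and r, the two candidates per match and the constant direction of preference are all assumed. The row q = 1 describes a systematic preference in every pair and is an extreme.

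**The case against.** The strongest reply is that the phrase in section 4.5 is awkward English for comparability. Sections 1.2 and 4.3 use that idea, and a matched group is what all three appear to want. This is the likelier meaning. It removes any suggestion of intent, but it does not make the trigger measurable or reconcile the three sections, and section 4.5 is where recruitment is actually set out.

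A reader might go further and infer that the protocol lets controls be added or swapped until the groups differ. The documents do not support that. Section 6.8 places analysis and comparison after examination and documentation, group size is fixed at 60 (section 4.4), section 1.2 speaks only of further controls, and no section provides for an interim look or for replacing an examined control. A reader might also infer that the 5% error level is lost. That cannot be shown, because nothing in the protocol gives the inputs of the illustration.

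Other parts of the reply also stand. Choosing a control after the index patient is inherent in individual matching. A single examiner avoids differences between examiners. A control's scores are unknown before the study examination. The undefined multimorbidity criterion applies to both groups, so it matters here only because it is one more judgement made by the same person.

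What remains is that age and gender matching decides who is eligible, but not which eligible person is taken or from which source.

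**Conclusion.** The point holds as a defect in the recruitment rule, not as evidence of bias. Sections 1.2, 4.3 and 4.5 contradict each other on when the control source may change and on the status of the tinnitus centre, and none states a measurable condition. Because one unmasked examiner recruits and scores both groups and chooses controls after the patients have been examined, section 4.5 followed as written leaves selection open to influence from oral findings or from the look of the comparison.

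The size is unknown. The illustration shows only that a modest preference would matter at 60 per group: shifts of about 0.08 to 0.20 SD correspond to false-positive rates of about 7% to 19% under the stated assumptions. The contradiction and the missing rule do not depend on those assumptions. The change should be made because it is cheap and because this kind of bias cannot be repaired in the analysis.

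**What to change.** Put one rule, in identical words, in sections 1.2, 4.3 and 4.5:

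- For each patient, approach the first consecutive ENT attender who meets the age and sex match, within a stated age tolerance, and the eligibility criteria.
- Settle eligibility, including a stated definition of multimorbidity, before the oral examination.
- Move to the next source, in a fixed order, only when no match has been found within a stated time. Never move because of oral findings or a comparison of results.
- Keep a short screening log: persons approached, source, and reason not enrolled.
- Report the patient-control comparison by control source.

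The rule takes the choice away from the examiner, so a second person is not essential. Where staff allow, having someone without access to the oral findings select controls would be stronger. If recruitment is already complete, the report should state how controls were in fact chosen and from which source, and give results by source.

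The cost is a change of wording and a one-page log, with no added participants. The downside is less freedom in recruiting and some slower matches.
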